#### 1.2.3. Qualitative Part of the Study

Objective: To analyse experiences and opinions on the WSJ of people aged 14 to 25 from a social constructivist perspective (is a theoretical and methodological approach that supports the collective generation of meanings through language and social interaction [32]). Participants will be of different sexes, gender identities, sexual orientations and socioeconomic conditions, from urban, semirural and rural areas of Catalonia. WSJ knowledge, use, usability, accessibility (digital equity-is the fair distribution of digital resources throughout the entire population [33]-), usefulness and relevance of content will be assessed in order to improve and adapt its resources.

#### 1.2.4. Quantitative Part of the Study

General objective: To understand how the youth population of Catalonia evaluates the WSJ.

Specific objectives:To determine what content of the WSJ receives the best rating by young people.To identify whether assessment of content and usability of the WSJ varies according to the following factors: age, sex, gender identity, sexual orientation, culture of origin, socioeconomic status, area of residence (urban, semiurban or rural) and motivation for consulting the website (of their own accord or suggested by a professional).To identify whether assessment of content of the WSJ is different in young people that had previously used it.To assess if having previously consulted the ASSIR unit is associated with a different assessment of the WSJ content.To determine if the target population knows about the WSJ, and what percentage use it and consider it useful.To evaluate if socioeconomic conditions determine the use of paper vs. digital questionnaires.To determine if young people in Catalonia visit other affective-sex education websites, and which are the most popular.To determine if young people in Catalonia follow any influencers for affective-sexual education, and which influencers are the most popular.To determine the percentage of young people in Catalonia that visit pornography websites.

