### 2.3. Sample/Participants

Participants will be teenagers and young adults aged 14 to 25 able to express themselves in one of the two official languages of Catalonia (Catalan or Spanish). We will exclude people who do not wish to participate in the investigation and people under 16 who wish to participate but whose parents/legal guardians do not sign the informed consent form. 

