#### 2.3.2. Quantitative Part of the Study

We have devised three methods for participant recruitment: (1) convenience sampling will be used in education centres (high schools, vocational training schools, training and insertion programs and universities); (2) consecutive sampling will be used to recruit young people who consult the ASSIR units; (3) young people who access the WSJ of their own accord will be invited to participate. These three methods will be used to invite participants to join the study; participation will be voluntary. Recruitment is more fully developed in the data collection Section 2.4.2.

Based on the size of the effect of the differences in the assessment of the WSJ contents, and depending on whether they consulted the website of their own accord or not, a total sample of 776 participants will be required, accepting an alpha risk of 0.05 and a beta risk of 0.2 in a two-sided test. Up to 388 subjects will be necessary in the first group and 388 in the second to find a statistically significant proportion difference, expected to be of 0.5 in group 1 and 0.4 in group 2.

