Due to COVID-19, Microsoft Forms and Microsoft Teams software might be used. In this case, we will guarantee data protection, in accordance with the Regulation (EU) 2016/679 of the European Parliament and Council of April 27 on Data Protection (RGPD) and the Spanish Organic Law 3/2018 of December 5, on the Protection of Personal Data and guarantee of digital rights. The online questionnaire can only be answered by people aged 16 and over since the necessary consent cannot be obtained from children under 16. Consequently, the first question in the online questionnaire is if they agree to answer it, and the second if they are 16 or older. Responses from those under 16 will be collected using the paper questionnaire at the education centres and ASSIR units.

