#### 2.6.2. Quantitative Part of the Study

We will perform a descriptive analysis of all variables, using frequencies and percentages for categorical variables and mean and standard deviation for age and years living in Spain. Familiarity with the website will be summarized with a percentage and confidence interval. The bivariant analysis will be performed using Pearson’s chi-squared test or Fisher’s exact test to find associations between the assessment of WSJ and the sociodemographic variables. If the bivariant analysis shows any associations, a multivariant analysis using a regression model with assessment of WSJ as the outcome variable is planned. The anlaysis will be performed disaggregating by gender. Significance level is set at 5%. SPSS statistical package for Windows, version 25.0, will be used for all analyses.

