### Limitations

Often, young people find it difficult to make commitments, and thus effective recruitment becomes more complex. Double consent, required of people under the age of 16, demands more resources and further hinders participation. Despite these limitations and in agreement with the literature, the proposed methodology is considered adequate.

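### The objective on pornography-site use asks for a rate among young people in Catalonia, but a pooled percentage from this sample depends on the recruitment mix and cannot supply it

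*Protocol article*

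**What the plan says.** Three of the specific objectives in section 1.2.4 of the protocol article do not concern the website itself:

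- Pornography: "To determine the percentage of young people in Catalonia that visit pornography websites".
- Other sites: "To determine if young people in Catalonia visit other affective-sex education websites, and which are the most popular".
- Influencers: "To determine if young people in Catalonia follow any influencers for affective-sexual education, and which influencers are the most popular".

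Section 2.3 gives the age range: "Participants will be teenagers and young adults aged 14 to 25".

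Section 2.3.2 lists three voluntary routes. In the first, "convenience sampling will be used in education centres". The second takes consecutive ASSIR users, and the third takes people who reach the website unprompted. The required size is 776, or 388 per group, to compare an expected 0.5 with 0.4. Section 2.4.2 says that the two groups are those directed to the survey by a professional (education centres and ASSIR) and those who came by themselves.

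On age, section 2.5 says: "The online questionnaire can only be answered by people aged 16 and over". Those under 16 answer on paper at education centres and ASSIR units, with a form signed by a parent or guardian. The Limitations section treats this as a burden on recruitment: "Double consent, required of people under the age of 16, demands more resources and further hinders participation". It does not mention representativeness.

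On analysis, section 2.6.2 says: "We will perform a descriptive analysis of all variables, using frequencies and percentages for categorical variables". The only breakdown named is by gender. The bivariate tests and the regression model concern assessment of the website.

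**The concern.** The pornography objective names a population quantity. The design supplies three voluntary groups whose relative sizes come from recruitment and from a power calculation for a different question. The analysis as described pools them. If the behaviour differs between school students, sexual-health service users and visitors to a sex-education website, or between younger and older adolescents, the pooled percentage reflects the proportions recruited. Disaggregating by gender removes neither dependence.

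At stake is how the figure will be read. A percentage reported against this objective invites citation as the rate for Catalan youth aged 14 to 25, and nothing in Limitations would warn a reader off.

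**Working it through.** **1. The plan's own figure.** Inputs from section 2.3.2: 0.5 vs 0.4, two-sided alpha 0.05, beta 0.2, equal groups. With pooled variance and no continuity correction,

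n = [1.96·√(2·0.45·0.55) + 0.842·√(0.5·0.5 + 0.4·0.6)]² / 0.1² = 387.3, rounded up to 388 per group, 776 in total.

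This matches the plan, so the arithmetic is sound. It serves a comparison between routes, not the estimation of a prevalence.

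**2. What a pooled percentage estimates.** With route shares w and route-specific rates p, the pooled figure is Σ w·p. Its bias for the population is Σ w·p minus the true population rate. The documents give no route-specific rates, no share of 14–25-year-olds who use ASSIR or the website, and no population rate. The bias therefore cannot be computed, in size or in sign.

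**3. Sensitivity to mix alone (rates assumed).** Hold the website group at half, as it would be if 388 and 388 were both met exactly. Let ASSIR vary from 10% to 40% of the total, with education centres making up the rest. Rates are in the order website/ASSIR/school.

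- Rates 50/45/40: 0.5·50 + 0.1·45 + 0.4·40 = 45.5%, and 0.5·50 + 0.4·45 + 0.1·40 = 47.0%. Shift: 1.5 points.
- Rates 70/60/40: 0.5·70 + 0.1·60 + 0.4·40 = 57.0%, and 0.5·70 + 0.4·60 + 0.1·40 = 63.0%. Shift: 6 points.

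**4. Age (rates assumed).** With equal single-year cohorts, ages 14–15 are 2/12 = 16.7% of the range. The website route is an online link, so it can contain none of them. If they hold their population share in the other half, their pooled share is 1/12 = 8.3%. The error is (sample share − 2/12)·(rate at 14–15 − rate at 16–25):

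- 30% vs 70%: (−1/12)·(−40) = +3.3 points.
- 40% vs 60%: (−1/12)·(−20) = +1.7 points.
- If schools over-recruit them to 30% of the sample, at 40% vs 70%: (0.30 − 0.167)·(−30) = −4.0 points.

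The sign depends on recruitment.

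**5. Benchmark.** The 95% sampling half-width at n=776 and p=0.5 is 1.96·√(0.25/776) = 3.5 points.

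**The case against.** Several objections have force.

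- *Only one objective says percentage.* True. The other two ask whether young people visit other sites or follow influencers, and which are most popular. A reader might infer that all three are stated as percentages, but the wording supports that only for pornography. The other two are affected because section 2.6.2 would report them in the same way.
- *The article condenses a fuller plan, and the word crude does not appear.* Also true. The absence of an interval or an age table for a descriptive item is not the point here. The point is that the objective, the recruitment routes, the age bar and the analysis are all stated in this article and do not fit together. No unseen analysis plan can turn this into a probability sample.
- *The 388 and 388 are a required size, not a quota.* Correct. The realised split may differ, but recruitment would still set it.
- *The age effect is small.* With the assumed rates and a proportional share in the invited half, it is 1.7 to 3.3 points, below the 3.5-point half-width, and it can reverse. It would be wrong to claim that the age bar inflates the figure.
- *These are not the main results.* The general objective is evaluation of the website, and the design is openly descriptive and partly convenience-based. That limits the stakes, but it does not reconcile the objective with the sample.

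**Conclusion.** The point stands as a mismatch between objective and sample. As written, the pooled percentage depends on the recruitment mix and does not estimate the rate among young people in Catalonia. That conclusion does not rest on the assumed rates, which only show scale: changing the ASSIR/school mix alone moves the figure by about 1.5 to 6 points, against 3.5 points of sampling error. These shifts are not estimates of bias, whose size and direction the documents leave undetermined.

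A reader might join the lowest and highest results in the working and infer that recruitment mix could move the figure from 45.5% to 63%. That is not supported, because the two ends use different assumed rates as well as different mixes. The change is worth making because it is cheap and prevents a misreading.

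**What to change.** - **Section 2.6.2:** report the three outcomes with 95% confidence intervals by recruitment route and, as a separate breakdown, by age band (14–15, 16–18, 19–25). Do not present a single pooled figure as the rate for Catalonia.
- **Section 1.2.4:** reword the three objectives as applying to survey respondents.
- **Limitations:** state that the sample is non-probability, and that the online age bar and parental consent select which 14–15-year-olds answer.

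Two extensions are best avoided. Standardising to the Catalan age and sex distribution cannot remove selection through services or the website, and could lend the figure false authority. Crossing route, age band and two genders gives 3·3·2 = 18 cells, of which the two website cells for ages 14–15 are empty by design. The other 16 would average 776/16 = 48.5 people, with a half-width of 1.96·√(0.25/48.5) = 14 points.

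The cost is wording and tabulation. Age and access route are among the listed variables. Section 2.4.2 describes the route mainly as professional-directed versus own accord, so the team should confirm that education centres and ASSIR units can be told apart. The downside is wider intervals: 1.96·√(0.25/388) = 5.0 points for a group of 388, and 1.96·√(0.25/194) = 7.0 points for each of schools and ASSIR if they split the invited group evenly (an assumption). The claim also becomes more modest.

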## 2. Materials and Methods

### 2.1. Design

We will use a parallel convergent triangulation design [32] and concomitantly implement a qualitative and quantitative phase. When these phases finish, we will prepare a single report triangulating the results of the two phases. Approval dates for this protocol were February 2017 and July 2020 for the qualitative part and entire mixed-methods part of the project, respectively. The study will last three years and participants will be young people living in Catalonia.

#### 2.1.1. Qualitative Part of the Study

The study will adopt an explanatory/interpretative model within a social constructivist framework. It will aim to describe and interpret social meanings generated collectively, i.e., the experiences and opinions of young people regarding the WSJ, affective-sexual education and their experience and needs regarding their sexuality. Investigators will have to discriminate between the hegemonic and counter-hegemonic discourses that originate from these social constructs [32,34].

#### 2.1.2. Quantitative Part of the Study

This is an observational, descriptive and cross-sectional quantitative study, for which an “ad hoc” questionnaire has been created.

### 2.2. Researchers’ Description

Since this protocol uses mixed methods, how the researchers’ background might influence the analysis must be explained. The principal investigator and most researchers are midwives working at ASSIR units, where they offer affective-sexual education to young people at individual consultations as well as in the community, at education centres and various associations and public spaces.

### 2.3. Sample/Participants

Participants will be teenagers and young adults aged 14 to 25 able to express themselves in one of the two official languages of Catalonia (Catalan or Spanish). We will exclude people who do not wish to participate in the investigation and people under 16 who wish to participate but whose parents/legal guardians do not sign the informed consent form. 

#### 2.3.1. Qualitative Part of the Study

The sampling will be theoretical. Participants will have to meet different profiles defined by representativeness criteria specified by the research team in order to provide heterogeneity to the sample and until reaching theoretical saturation of technical data. The representativeness criteria are age (two groups: 14–18 and 19–25), rural and city areas, different socioeconomic conditions, all sexes (male/female/intersex), different gender identities (male, female, transgender, non-binary, fluid and other) and different sexual orientations (heterosexual, homosexual, plurisexual, asexual).

#### 2.3.2. Quantitative Part of the Study

We have devised three methods for participant recruitment: (1) convenience sampling will be used in education centres (high schools, vocational training schools, training and insertion programs and universities); (2) consecutive sampling will be used to recruit young people who consult the ASSIR units; (3) young people who access the WSJ of their own accord will be invited to participate. These three methods will be used to invite participants to join the study; participation will be voluntary. Recruitment is more fully developed in the data collection Section 2.4.2.

Based on the size of the effect of the differences in the assessment of the WSJ contents, and depending on whether they consulted the website of their own accord or not, a total sample of 776 participants will be required, accepting an alpha risk of 0.05 and a beta risk of 0.2 in a two-sided test. Up to 388 subjects will be necessary in the first group and 388 in the second to find a statistically significant proportion difference, expected to be of 0.5 in group 1 and 0.4 in group 2.

### 2.4. Data Collection

#### 2.4.1. Qualitative Part of the Study

Focus groups and in-depth interviews will be used to collect information. A focus group consists of a group interview led by a moderator using a topic/interview script (the script of this project is available in Supplementary Material Table S1), with the additional participation of an observer [35]. Focus groups are based on the concept that group interaction facilitates reflection on individual and shared perspectives. They last between 90 and 120 min and include 4 to 12 people [36]. Focus groups will be audio- and video-recorded, and the recording will be stored in an encrypted file that prevents participant identification. The recordings obtained will be confidential, accessible only by informants and the research team and eliminated after one year. We have planned to conduct 10 focus groups, although this number might change based on the sufficiency and relevance of the information obtained, until saturation is achieved [32]. In-depth individual interviews will be used when participants feel they need more confidentiality and in cases of difficulty recruiting enough young people with specific profiles.

In the context of COVID-19, we might need to conduct virtual focus groups and/or individual interviews using the Microsoft Teams platform.

The recruitment of participants will take place at the ASSIR units during individual consultations, Youth Afternoons, the educational centres collaborating on the study and various youth associations, including those advocating for affective-sexual and gender diversity rights across all of Catalonia. Researchers will select potential informants and explain that they will receive a call from the principal investigator of the project, inviting them to participate in a group interview.

#### 2.4.2. Quantitative Part of the Study

In the context of COVID-19, we have both an online (Microsoft Forms) and paper version of the questionnaire (Teleform). The online questionnaire can be accessed via direct link or QR code. The questionnaire consists of 24 closed questions and 2 open-ended questions. The questionaire is available in Supplementary Material (Figure S1).

At the education centres: The recruiting researchers will communicate with these centres to disseminate the questionnaire among students. The centre directors will decide if their centre will use the online or paper questionnaire.At the ASSIR units: a wide network of professionals are also researchers that will recruit for the study. The study will be disseminated through posters in the waiting rooms and at the counter of each ASSIR unit. These posters will contain the study instructions and the QR code for the questionnaire so that young people can quickly download it to their mobile phone and answer it. There will also be a paper version of the questionnaire for people unable to access it digitally. Digital users of the ASSIR will be sent the link to the questionnaire with information to encourage them to answer on the same platform they used for the consultation (email, WhatsApp^®^, e-consultation).WSJ users who make email inquiries will automatically receive an email with the direct link to the questionnaire, encouraging them to participate after explaining that this is a study to evaluate the website. The study will be also advertised on the WSJ homepage through images with a direct link to the questionnaire.

Whatever the origin of the participant, the variables that will be evaluated for all the participants in the sample through the questionaire are the following:

Sociodemographic variables: age, sex, gender identity, sexual orientation, country/culture of origin, years of residence in Spain, postal code, socioeconomic condition of the postal code according to the Territorial Socio-Economic Index, city/rural/semirural residence, current job, ongoing studies, type of access to the questionnaire (electronic or paper).

Variables related to the WSJ: prior knowledge of the WSJ, use of the WSJ, usability of the WSJ, usefulness of the WSJ, rating of affective-sexual education content.

Variables related to social media: ability to access to digital resources, use of other webpages of affective-sexual education, following affective-sexual education influencers, use of pornography webpages.

Variables related to study recruitment: Participants from educational centers and ASSIR units will access the survey by indication of the professionals. The third contacting group will access it by themselves, without anyone’s indication. The sample calculation has been performed based on this variable.

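### The powered comparison is stated as motivation for consulting the website but coded by recruitment route, which misclassifies motivation and is tied to website use by design

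*Protocol article*

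**What the plan says.** All references are to the protocol article.

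- **Objective (1.2.4).** Among the factors that may affect the rating of the site is "motivation for consulting the website (of their own accord or suggested by a professional").
- **Sample size (2.3.2).** The calculation concerns differences in content rating "depending on whether they consulted the website of their own accord or not". It is made "accepting an alpha risk of 0.05 and a beta risk of 0.2 in a two-sided test", with proportions "expected to be of 0.5 in group 1 and 0.4 in group 2", and gives 388 per group and 776 in total. The text does not say which group is which.
- **Operational variable (2.4.2, recruitment variables).** "Participants from educational centers and ASSIR units will access the survey by indication of the professionals". The third recruitment group is described as reaching the survey unaided. Then: "The sample calculation has been performed based on this variable".
- **Recruitment procedure (2.4.2).** ASSIR units display posters with a QR code that attenders can scan themselves. For the third route, "WSJ users who make email inquiries will automatically receive an email with the direct link to the questionnaire", with encouragement to take part, and the homepage carries an advertisement.
- **Data recorded (2.4.2).** Prior knowledge and use of the website are collected from every participant, whatever the route.
- **Analysis (2.6.2).** Bivariate tests relate the website rating to sociodemographic variables. A regression follows if associations appear, with no covariates listed.
- **Age (2.5).** The online form is closed to those under 16, who answer on paper at education centres and ASSIR units.

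**The concern.** Two sections define the exposure as the reason for consulting the website. A third defines it as the way into the survey and says that the sample size rests on that. These are different facts about a person, and no variable listed in section 2.4.2 records the first.

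Three consequences follow:

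- **Misclassification in both directions.** A pupil or ASSIR attender who found the site alone is coded as professional indication. A site visitor sent there by a midwife or teacher is coded as own accord. If motivation matters, this dilutes the difference.
- **Association with website use.** The third route draws only on people already on the site or writing to it. The other two can include people who have never seen it. If users rate the site differently from non-users, the route comparison shows a difference even when motivation has no effect.
- **Association with age.** The third route operates through online links, so it should contain no 14- or 15-year-olds.

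At stake is the interpretation of the only comparison for which power is stated.

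**Working it through.** **1. Reproduce the plan's figure.** Inputs from section 2.3.2: p1 = 0.5, p2 = 0.4, two-sided alpha 0.05, power 0.80, equal groups. With the pooled null variance and no continuity correction,

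n = [1.960·√(2·p̄·(1−p̄)) + 0.842·√(p1(1−p1) + p2(1−p2))]² / (p1−p2)²

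with p̄ = 0.45:

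n = [1.960·√0.495 + 0.842·√0.49]² / 0.01 = [1.379 + 0.589]² / 0.01 ≈ 387.3, rounded up to 388 per group, 776 in total.

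This matches the protocol, and power at 388 per group is 0.801. The arithmetic is sound; the issue is what is being compared.

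**2. Compare the definitions.**

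| Section | What defines the groups |
|---|---|
| 1.2.4 | Why the website was consulted |
| 2.3.2 | Whether the website was consulted on own initiative |
| 2.4.2, recruitment variables | How the survey was reached |

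The route labels also fit poorly with the procedure in section 2.4.2. The group said to arrive unprompted includes email inquirers who are sent an invitation. The professional group includes people who may simply scan a poster.

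**3. Dilution (assumed rates).** Let m be the share of the professional route who in truth came to the site on their own, and k the share of the website route who were in truth sent by a professional. Take 0.5 as the true proportion for own accord and 0.4 for professional. Then

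p1 = 0.5 − 0.1k, p2 = 0.4 + 0.1m, power ≈ Φ{[(p1−p2)·√388 − 1.960·√(2p̄(1−p̄))] / √(p1(1−p1) + p2(1−p2))}.

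| m | k | Difference | Power at 388 per group | n per group for 80% |
|---|---|---|---|---|
| 0 | 0 | 0.10 | 80% | 388 |
| 10% | 0 | 0.09 | 71% | 480 |
| 10% | 10% | 0.08 | 61% | 606 |
| 20% | 10% | 0.07 | 50% | 794 |
| 20% | 20% | 0.06 | 39% | 1079 |

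**4. Confounding with use (assumed rates).** Suppose motivation has no effect, users rate at 0.5 and non-users at 0.4. With prior use u1 in the website route and u2 in the professional routes, the apparent difference is 0.1·(u1 − u2).

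- 80% versus 20%: 0.48 versus 0.42, a difference of 0.06, declared significant 39% of the time.
- 90% versus 10%: 0.49 versus 0.41, a difference of 0.08, declared significant 61% of the time.

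**5. Cost of adjusting for use.** With equal groups, the approximate variance inflation is 1/(1 − r²), where r² = 0.25·(u1−u2)² / [ū(1−ū)] and ū is the mean of u1 and u2.

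| Prior use by route | r² | Inflation | Total N for the same precision |
|---|---|---|---|
| 70% vs 30% | 0.16 | 1.19 | 924 |
| 80% vs 20% | 0.36 | 1.56 | 1213 |
| 90% vs 10% | 0.64 | 2.78 | 2156 |

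Adjustment is therefore feasible, at a price set by an overlap that the documents do not give. These inflations are for the route variable; a self-reported motivation item may be less closely tied to prior use.

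**The case against.** The best defence is that route and motivation coincide for many respondents. Someone who had never seen the site, and looks at it because a school or ASSIR unit invited them into the study, did come to it at a professional's suggestion and is coded correctly. Errors are then confined mainly to prior users in schools and ASSIR units and to referred visitors in the website route. One can also argue that a poster put up by an ASSIR unit is a form of professional indication. Both points limit the likely error rate, but neither makes the two definitions the same.

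It is also fair that the study is observational and descriptive, that motivation is one factor within one of several specific objectives, and that the regression covariates may be set out in an analysis plan that is not shown. That tempers the criticism of section 2.6.2. It does not touch the mismatch, because the article itself gives the operational definition and ties the sample size to it.

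A reader might go further and infer that motivation cannot be separated from prior website use. The documents do not support that: knowledge and use are recorded for everyone, the professional routes can contain prior users, and the homepage advertisement can reach first-time visitors. A reader might also infer that the objective "To assess if having previously consulted the ASSIR unit is associated with a different assessment of the WSJ content" has no variable behind it. The questionnaire is in a supplement that is not shown, so this cannot be established. For the same reason an item on motivation may already exist.

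**Conclusion.** The point holds as a mismatch of definition: the powered factor is named as motivation for consulting the website and coded as recruitment route. A route difference reported under the motivation label would be open to misclassification in both directions and to confounding with website use and age, and the article does not commit to dealing with either.

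The size is not known. The power figures of 61% and 39% require 10% and 20% error in both groups at once; 10% error in the professional routes alone leaves 71%. The spurious 6- to 8-point differences assume prior use of 80% versus 20% to 90% versus 10%, and a user effect borrowed from the planned 0.5 versus 0.4. All are illustrations of what could happen, not estimates of what will.

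**What to change.** 1. Define the exposure by each participant's own answer on how they came to consult the website (own initiative or a professional's suggestion), asked in all three routes. If the questionnaire already has such an item, use it and say so in section 2.4.2.
2. State in section 2.6.2 that the powered contrast will be stratified by, or adjusted for, prior use of the website and age.
3. State in section 2.3.2 that the 80% power applies to the unadjusted comparison.
4. If the item cannot be added (section 2.5 speaks of data collection in the past tense, so this may be the case), rename the contrast recruitment channel in sections 1.2.4, 2.3.2 and 2.4.2, adjust for prior use, and draw no conclusion about motivation.

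The cost is at most one closed question and some wording, plus a loss of precision from adjustment that depends on how far prior use overlaps between the groups. The fallback needs no new data but gives up the motivation question.
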